## **5.6 Physiological examination methods**

### **5.6.1 Intranasal application of oxytocin**

In a double-blind and placebo-controlled design, participants will take oxytocin (Syntocinon, Novartis, Basel, Switzerland) or placebo intranasally at the first laboratory appointment and then twice daily for 5 days after the first laboratory appointment:

During the 1st laboratory appointment, the subjects take 24 IU (3 sprays in each nostril) before the instruction of the standardized positive interaction/no interaction.

On the day of the first laboratory appointment, the test subjects are asked to spray 2 bursts of oxytocin or placebo into each nostril at 2 times on the following 5 days (together with the saliva vial measurements 4 & 5) (a total of  $2 \times 2 \times 4 \text{ IU} \times 2/\text{day} = 32 \text{ IU}$ ). This procedure is maintained on the following 5 measurement days at home. In total, the test subjects will therefore

ingest 1\*24 and 5 \* 32IU of either oxytocin or placebo (Ditzen, Schaer et al., 2009; [name] et al., 2003; Kosfeld et al., 2005).

#### **Compliance**

The compliance of the test subjects with regard to taking medication at home is queried via the handheld computer. Non-compliance means that the respondent does not take the investigational product or does not state whether he/she has taken it and whether any side effects have occurred. The data of this person are excluded from the data analyses. The investigator checks the entries during the visit at the end of the week and takes back the empty packs or unused units.

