##### **5.4.1 Research sample & power analysis**

100 heterosexual couples aged 25-45 years will be analyzed. Using G\*Power (Buchner, Faul, & Erdfelder, 1998), a sample size of N=76 was calculated for sub-study 1 with regard to the

main outcome variable "wound size" (see below) (effect  $f = .40$ ; power = .82,  $\alpha = .05$ ).  
The total N is set to  $N=100$  in order to be able to compensate for any dropouts.

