#### **5.4.4 Procedure**

After a telephone interview in which inclusion and exclusion criteria are clarified, the first laboratory appointment is arranged with interested test subjects. After reading the information and signing the written declaration of consent at the first appointment, the participants receive a participant code and are given an individualized link to the study website. This link will take the subjects to a survey including questionnaires on personality, relationship quality, and chronic stress, which they can complete online. The online presentation of the questionnaires is organized via "Unipark" ([www.unipark.com](http://www.unipark.com)), a program for individualized scientific online data collection. Access to the electronic program "Unipark" and thus to the data of the participant is password-protected, and only the study coordinator has access. "Unipark" was specially designed by Globalpark AG for online research and administration of research data sets. The use of the program requires a license. The electronically collected data are only relevant in connection with the data collected in the laboratory. The electronic and laboratory data are merged using the respondent code, which the respondents receive at the first laboratory appointment and enter at the start of the online questionnaire. The merging of the electronic and laboratory data only takes place after the written declaration of consent, which the test subjects date and sign in the laboratory. If this is not done or the experiment is cancelled, the electronic data will be destroyed immediately. The data on the handheld computer cannot be viewed directly and is sent to a password-protected e-mail address and managed from there. Only the study management has access to this e-mail address.

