### 5.6.3 Ecological Momentary Assessment (EMA)

The measurement of the psychological variables takes place on five days after the first laboratory appointment during four time points, the measurement of the saliva samples on six time points per day. The test subjects are contacted by a signal from the handheld computer (Palm Tungsten E2 handheld, or similar model) and asked to complete the questions on their current state of mind, stress and social interactions directly on the computer. The data is analysed using the freeware program "The Purdue Momentary Assessment Tool" (PMAT). The alarms are triggered at intervals of approximately three hours (Steptoe et al., 2008). In addition, the subjects are asked to perform 6 saliva measurements using salivettes (Salivette®, Sarstedt, Rommelsdorf, Germany) on all five days at the following times: immediately after waking up (measurement 1), 30 minutes after waking up (measurement 2), 2.5 hours after waking up (measurement 3), 8 hours after waking up (measurement 4), 12 hours after waking up (measurement 5) and before going to bed (measurement 6). Measurements 3-6 are compared with the four psychological measurements. The actual time of Salivette ingestion (and thus compliance with the study schedule) will be verified using electronic Aardex MEMS doses (Aardex Ltd, Zug, Switzerland). Drug accountability in sub-study 1 is ensured by asking the subjects at each measurement time point with the handheld computer whether they have taken the 2 sprays per nostril. In addition, the blinding table can be used to trace the batch number dispensed per subject. At the end of the study, the subjects must return the used nasal spray vials to the study coordinator so that the amount of nasal spray liquid actually taken can be verified. Compliance with Syntocinon® is recorded every day using a hand-held computer at and the intake of Syntocinon® is always recorded together with the saliva measurement, which is documented using the Aardex MEMS doses.

During the first laboratory appointment, the test subjects are explained how to use the EMA materials over the next five days. They also receive a written summary containing all the necessary information and telephone numbers for further questions.

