### **5.7.3 Statistical data analyses**

The primary endpoint of sub-study 1 is reached when 100 couples have been examined.

The group differences analyzed in sub study 1 (oxytocin vs. placebo, men vs. women) in relation to the main outcome variable wound healing will be evaluated using analyses of variance (ANOVAs). Associations between the repeated measures data of the EMA part of the study and the main outcome variable wound healing will be analyzed using hierarchical linear models (HLM) to account for the dependent data structure between partners.

The significance level of the data analysis is set at 5%. Individual missing data points are replaced by the group-specific mean value. The data of prematurely discontinuing study participants are analyzed for statistically significant differences with the remaining group.

All psychobiological data will only be analyzed after completion and termination of the sub-study in order to minimize inter-assay variance. Self-report and behavioral data will be analyzed in 6-month tranches.

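### Sub-study 1 removes non-compliers and non-reporters from the analyses after randomisation, with no threshold and no analysis as allocated

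*Protocol*

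**What the plan says.** The rule is in the compliance paragraph of Protocol section 5.6.1. Its trigger has two limbs: "Non-compliance means that the respondent does not take the investigational product or does not state whether he/she has taken it", and the second limb extends to side effects (the person "does not state whether he/she has taken it and whether any side effects have occurred"). The consequence is: "The data of this person are excluded from the data analyses". The paragraph does not say how many doses or entries must be missing, does not name an analysis set, and does not confine the rule to a secondary analysis.

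The home spray is used "then twice daily for 5 days after the first laboratory appointment". Section 5.6.3 describes accountability as "asking the subjects at each measurement time point with the handheld computer whether they have taken the 2 sprays per nostril", and adds that returned vials let the amount actually used be checked.

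Section 5.7.3 sets out the analysis. It offers mean imputation for single missing values and one sentence on people who stop early: "The data of prematurely discontinuing study participants are analyzed for statistically significant differences with the remaining group". It does not say that non-compliers stay in the comparison of arms.

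Allocation is by couple: section 5.4 assigns 25 couples to each of four arms, and section 5.4.4 gives both partners the same preparation. Section 5.4.1 says "a sample size of N=76 was calculated for sub-study 1 with regard to the" wound-size outcome, then raises the total to 100 to cover dropouts. Exclusions for non-compliance are not mentioned there.

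The point concerns sub-study 1 only. In sub-study 2 intake is observed directly (section 6.5.2).

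**The concern.** Randomisation makes the arms comparable when couples are allocated. A rule that removes people for what they do or report during the following week gives up that protection. The protocol itself supplies a route from arm to exclusion to outcome: section 5.2 expects oxytocin to change couple interaction and stress, and section 4.2.3 describes stress as slowing healing. Stress and couple interaction could plausibly also affect whether someone sprays on time or answers the handheld. If so, the people left in each arm would differ in ways related to wound size, and the oxytocin estimate could shift in either direction.

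Two further costs follow from the wording. The reporting limb removes a person who may have taken every dose but left an entry blank, although the wound may have been measured and the returned vial can show use. And exclusion applies to the person while allocation applies to the couple. One partner can go while the other stays, and the protocol does not say what then happens to the remaining partner.

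**Working it through.** **1. The plan's own sample size.** Inputs from section 5.4.1: f = 0.40, alpha = 0.05, power 0.82, N = 76. For a four-group ANOVA, the noncentrality is f² × N = 0.16 × 76 = 12.16 with 3 and 72 degrees of freedom, and power is 0.823. The smallest N reaching 0.82 is 76, so the stated figure reproduces as a four-group omnibus test. A 1-df drug contrast would need only 54 (power 0.931 at 76). N is read as couples because it is raised to 100 couples. The margin is then 100 − 76 = 24 couples, or 24%.

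**2. Exposure to the rule.** Home doses: 2 per day × 5 days = 10 per person, 20 per couple. Let q be the chance that a dose is missed or unrecorded. The protocol gives no value, so q is assumed, with misses taken as independent.

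**3. Where the margin runs out, under three readings of the rule.**

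- One miss removes the couple: (1 − q)^20 = 0.76, so q = 1 − 0.76^(1/20) = 1.36%.
- One miss removes only the person: (1 − q)^10 = 0.76, so q = 1 − 0.76^(1/10) = 2.7%. At that point 100 × 0.76² = 58 couples are intact, 100 × 2 × 0.76 × 0.24 = 36 have lost one partner, and 100 × 0.24² = 6 have lost both.
- Only whole-person non-compliance (share d of persons) counts, and the couple is then dropped: (1 − d)² = 0.76, so d = 1 − 0.76^(1/2) = 12.8%.

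**4. Range under the strictest reading (complete couples, four-group test).**

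| q | Couples left of 100 | Power |
|---|---|---|
| 0.5% | 90 | 0.89 |
| 1% | 82 | 0.855 |
| 2% | 67 | 0.76 |
| 3% | 54 | 0.65 |
| 5% | 36 | 0.45 |

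Under the whole-person reading, d = 10% leaves 100 × 0.9² = 81 couples and d = 15% leaves 100 × 0.85² = 72.

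**5. Bias.** This is an illustration by simulation with assumed inputs: no true effect, 50 units per drug group, a two-sample comparison at 5%, and a latent tendency to be excluded that is correlated with the outcome.

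| Exclusion by group | Correlation | Type I error | Spurious shift (absolute) |
|---|---|---|---|
| 24% and 24% | 0.5 | 0.050 | about 0 |
| 14% and 34% | 0.3 | 0.067 | 0.09 SD |
| 14% and 34% | 0.5 | 0.099 | 0.15 SD |
| 4% and 44% | 0.5 | 0.26 | 0.31 SD |

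Equal exclusion costs precision only. Unequal, outcome-related exclusion also costs validity.

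**6. After the change.** With all 100 couples analysed, noncentrality is 0.16 × 100 = 16 and four-group power is 0.924 (0.977 for a 1-df drug contrast). The margin is then spent only on couples with no final wound measurement.

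**The case against.** **One missed dose.** A reader might infer that a single missed or unrecorded dose always removes a person. The documents do not say so. The query is made at each occasion and no tolerance is stated, which makes that reading possible. Against it, section 5.4.3 speaks of refusing regular use, and section 5.7.3 imputes isolated missing values, so a single gap could be meant to be tolerated. What stands is that no threshold is fixed. A SAP could supply a cut-off, but it could not keep non-compliers in the main analysis without contradicting the protocol.

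**Size of the loss.** The 1.4% figure deletes whole couples, whereas the text removes only the person. Misses probably cluster within people and couples, which would leave more of both at the same average rate. A 1-df oxytocin contrast, which section 5.7.3 names, still has 0.82 power with 54 couples, so it tolerates q of about 3%. If N = 76 meant persons out of 200, the limit would be about 9%. All of this stands, and it makes the loss conditional.

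**Bias.** Drug allocation stays blinded until data collection ends, so staff should not be able to select by drug, and section 7.3.1 expects no side effects. A reader might add that the burden of the interaction instruction biases the drug comparison. In the 2×2 design it is balanced across oxytocin and placebo, so by itself it does not. Blinding does not remove selection that arises from the drug's own effects, so the possibility of bias remains, with unknown size.

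**Data destruction.** A reader might see a conflict between section 5.7.3's comparison of early stoppers and section 5.4.4: "If this is not done or the experiment is cancelled, the electronic data will be destroyed immediately". The documents do not establish one. That sentence concerns electronic data and follows text on merging online questionnaires after consent, and it is unclear what cancelling the experiment refers to. Wound measurements are laboratory data and would still be available.

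**Conclusion.** The point holds as a fault in who enters the main comparison. The protocol prescribes an open-ended exclusion after randomisation, based on dosing and reporting, and offers no analysis as allocated beside it. This opens the oxytocin comparison to bias if exclusion differs by arm and is related to healing. It also wastes wound data and can break up the randomised couple.

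The direction and size of any bias cannot be stated from the documents. Nor can it be said that the reserve will be exhausted: no non-compliance rate is given, and the limits of about 1.4% of doses, 2.7% of doses and 12.8% of persons rest on the four-group reading of N = 76 couples, on independence (of misses for the first two, of partners for the third), and on how the rule is applied. The need to change the sentence does not depend on which limit is right.

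**What to change.** Replace the exclusion sentence in the compliance paragraph of section 5.6.1 with: *The primary analysis includes all randomised couples in the arm allocated, using every wound measurement obtained, regardless of dosing or diary compliance.*

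Use compliance only to define a per-protocol sensitivity analysis. Fix its cut-off before unblinding, treat a dose not taken separately from a dose not recorded, use the returned-vial amounts as well as the handheld entries, and state what happens to the partner of an excluded person.

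Keep the already scheduled final wound measurement for non-compliers who remain in the study. Recalling everyone who has left would go further: it adds a procedure and would have to fit the terminations in section 5.4.3 and the right to withdraw, so it is not part of this change.

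The cost is a short amendment, which section 3.1 makes subject to ethics committee and authority approval. No new measurement is needed. The estimate will reflect actual compliance and may be slightly diluted.

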#### **Pre-treatment and concomitant therapy**

No other treatments or medications are permitted during the study. Any concomitant therapies will be requested at the start of the study. All possible concomitant and/or emergency medication(s) must be documented in the CRF.

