#### *Exclusion criteria*

- Indications that the participant is unlikely to comply with the test plan (e.g. unwillingness to cooperate)
- Participation in another clinical trial within the last 4 weeks prior to inclusion
- Skin disease
- Accident with neurological sequelae
- Allergies or a history of known hypersensitivity to one of the drugs used or their ingredients, or to drugs with a similar chemical structure
- UV-B irradiation in the last 3 months before the examination
- Taking medication
- Drug use, addiction or other illnesses that do not allow the person concerned to the nature, scope and possible consequences of the clinical trial
- Overweight or underweight
- Daily alcohol consumption ( $> 60g$  alcohol, equivalent to approx. 7.5 dl wine or 2 litres beer per day)
- No participation of the Investigator or his/her family members, employees or other dependent persons
- Women: Pregnancy (for instructions on the double barrier to prevent pregnancy, see subject information) or intention to become pregnant during the course of the study

- Women: Breastfeeding

These criteria are queried with the interested participants in a telephone interview. No personal details are recorded during this telephone interview, so that no personal data can be linked to the inclusion or exclusion criteria before the consent form is signed. An appointment for the study is arranged with interested and suitable test subjects, at which the inclusion and exclusion criteria are discussed again and the test subjects sign the declaration of consent.

For this study, it is essential that certain things are controlled, as these activities or factors influence the measured values and may make them unusable. For this reason, the test subjects were asked to follow the instructions bellow:

- Do not drink coffee or other caffeinated drinks (cola, energy drinks, etc.), black tea or alcohol on the afternoon of the first laboratory appointment (approx. from 3 pm),
- Do not engage in excessive sport on the day of the examination,
- Do not smoke immediately before the 1st laboratory appointment,
- No physical exertion (cycling etc.) immediately before the 1st laboratory appointment,
- Do not eat anything heavy immediately before the 1st lab appointment.

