### 5.4.3 Recruitment

The test subjects are recruited via circular mail from the mailing list for the recruitment of test subjects of the Psychological Institute of the University of Zurich, the description of the study in public media (ronorp, 20Minuten, NZZ), notices and websites for the recruitment of test subjects and receive CHF 500 per couple as compensation for participation. All couples will receive individual feedback on their results. On request, couples will be given the option of psychological counselling at the Outpatient Clinic for Cognitive Behavioral Therapy and Behavioral Medicine at the University of Zurich.

- Subjects may terminate their participation in the study at any time without giving reasons and without any disadvantage.
- The principal investigator may terminate a subject's participation in the study after weighing up the risk/benefit ratio. Possible reasons are
  - Health problems and adverse events
  - Refusal to use the nasal spray regularly
- Reasons for stopping the nasal spray immediately include

- Pregnancy
- Hypersensitivity to oxytocin or an excipient of the nasal spray
- Participation in the study must be terminated in the following cases:
  - If it subsequently transpires that the required inclusion criteria do not apply or at least one exclusion criterion applies
  - Cancellation of the investigation

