#### **7.3.2 Suction blister application, measurement of wound fluid and measurement of the wound**

The application of the suction blisters to the arm results in a small wound. This wound may cause slight pain. Removing the wound fluid can also be painful. In very rare cases, the wound may become inflamed, be painful for longer and leave scars. No medical side effects are to be expected when the wound is measured after one week.

We will apply the suction blisters and measure the wound fluid in accordance with international standards and under sterile conditions. In addition, the test subjects are asked to report any symptoms or pain to us immediately so that they can be treated.

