### 7.3.3 For women of childbearing age

As Syntocinon spray can lead to uterine contractions towards the end of a pregnancy and can trigger milk production, it must not be used in pregnancy except for these medical implications. We therefore carry out a standard pregnancy test on all female participants before the start of the study. In the study, a double-barrier method of contraception is used to prevent pregnancy, i.e. the study participants use two reliable methods of contraception during the study (in sub-study 1: pill in combination with -, otherwise double mechanical contraception, e.g. diaphragm, IUD etc. in combination with condoms). Patients who become pregnant during the study must inform their doctor immediately and may not continue to participate in the study. In this case, they are asked to consult a specialist doctor so that specialist medical care is ensured and to provide information on the course and outcome of the pregnancy (see also 7.5.1). Women who are breastfeeding are excluded from participation in the study. In order to rule out the possibility of pregnancy occurring during the study in everyday life, we examine all our participants during the luteal phase (day 16 - 28 of the menstrual cycle).

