## 1232 **9 Insurance**

1233 The insurance is covered by the liability insurance for the University of Zurich, which was  
1234 taken out specifically for this study. This covers all damages in connection with the study.  
1235 Study participants must strictly adhere to the instructions of the study personnel. Furthermore,  
1236 they may not undergo any other medical treatment during the clinical trial without the consent  
1237 of the investigator (with the exception of emergencies). They must inform the investigator

1238 immediately of any emergency treatment. If health problems or other damage occur during or  
1239 after participation in the study, the investigator must be informed. A copy of the insurance  
1240 certificate will be filed in the trial centre folder.

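### The ban on all other medication conflicts with the promised treatment of wound symptoms and leaves the pill unclear, and nothing keeps a participant whose participation is ended early in the one-week wound measurement

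*Protocol*

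**What the plan says.** **Treatment during the study.** Protocol 5.6.1, in the paragraph on pre-treatment and concomitant therapy, says "No other treatments or medications are permitted during the study". The same paragraph continues: "All possible concomitant and/or emergency medication(s) must be documented in the CRF". It names no other consequence of taking medication.

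Section 7.3.2 says of the suction blister wound that "the test subjects are asked to report any symptoms or pain to us immediately so that they can be treated". It describes slight pain as possible, and inflammation, longer-lasting pain and scars as very rare.

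Section 9 (Insurance) says that "they may not undergo any other medical treatment during the clinical trial without the consent" of the investigator, with an exception for emergencies.

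**Eligibility.** The sub-study 1 exclusion criteria (5.4.2) list "Taking medication" without qualification. Section 7.3.3, on contraception, specifies "in sub-study 1: pill in combination with" a second method, and 7.3.4 repeats this in the section for men. The sub-study 2 list (6.4.2) has the same medication criterion and, as a separate item, hormonal contraception. The sub-study 1 list has no such separate item.

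**Ending participation.** Section 5.4.3 lets the principal investigator end participation for health problems and adverse events. It makes ending participation mandatory in this case: "If it subsequently transpires that the required inclusion criteria do not apply or at least one exclusion criterion applies".

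**Outcome and analysis.** The main outcome is the reduction in wound size one week after application (5.3). Section 5.7.3 replaces individual missing data points by the group-specific mean and compares people who discontinue with the remaining group.

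**The concern.** The study itself creates the wound, so a participant who needs something for it is foreseeable. Staff cannot follow the ban in 5.6.1 and the promise in 7.3.2 together as they are worded. On eligibility, two recruiters could reach different decisions about the same woman on the pill.

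The statistical stake is the main outcome. A wound that becomes inflamed or stays painful may also be one that heals slowly. If participation ends because of it and the one-week measurement is not taken, the missing value depends on the outcome. If oxytocin does speed healing, more such participants would be lost under placebo, and the observed benefit would shrink.

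**Working it through.** **1. The treatment passages side by side**

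| Place | Other treatment or medication |
|---|---|
| 5.6.1, first sentence of the paragraph | none permitted |
| 5.6.1, last sentence of the paragraph | concomitant and emergency medication to be recorded |
| 7.3.2 | wound symptoms or pain will be treated |
| 9 | possible with the investigator's consent, or in an emergency |

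The first row is absolute and the other three presuppose exceptions. They cannot all stand as written.

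**2. Routes to a missing one-week wound size**

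- Discretionary: health problems and adverse events (5.4.3). A wound complication fits directly.
- Mandatory, on a literal reading only: someone given medication now meets an exclusion criterion (5.4.2 with 5.4.3).

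Neither route is followed by a statement that the participant returns for the wound measurement. The follow-up visit in 7.9, up to 30 days after the end of treatment, examines health status for persistent events. It is not described as collecting the wound outcome.

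**3. Would the missing-data rule repair the loss?**

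Suppose *m* of *n* values in an arm are missing and are replaced by the mean *r* of those retained. The arm mean is then [(n − m)·r + m·r]/n = r, the same as if they had been dropped. The sum of squares does not change, while its divisor grows from n − m − 1 to n − 1, so the variance is understated. The rule therefore leaves any selection bias in place.

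**4. Does the dropout reserve cover it?**

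The plan's figure reproduces. With four groups, 3 numerator degrees of freedom, f = 0.40, α = 0.05 and N = 76, the noncentrality is 76 × 0.40² = 12.16 and power is 0.823 (stated: 0.82). Raising N to 100 allows a loss of 24/100 = 24% before power falls to that level. The reserve covers numbers lost. It does not correct selective loss.

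**5. Illustrative size**

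Assumptions, none of them from the protocol: one-week wound size is normal with SD 1; the true oxytocin benefit is δ; every wound above one common threshold *t* is lost; *t* is the placebo quantile that leaves a fraction *p* above it.

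- Retained placebo mean: −φ(t)/Φ(t)
- Retained oxytocin mean: −δ − φ(t + δ)/Φ(t + δ)
- Attenuation: 1 − (difference of retained means)/δ

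Example, δ = 0.5 and p = 10%: t = 1.282, placebo mean −0.195, oxytocin mean −0.585, difference 0.390. Attenuation is 1 − 0.390/0.5 = 22%. Placebo loses 10% and oxytocin 3.7%.

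| Placebo lost (p) | Attenuation, δ = 0.5 | Attenuation, δ = 0.8 |
|---|---|---|
| 0.1% | 0.55% | 0.4% |
| 0.5% | 2.2% | 1.7% |
| 1% | 3.9% | 3.0% |
| 5% | 14% | 11% |
| 10% | 22% | 19% |
| 20% | 34% | 30% |

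The value δ = 0.8 is f = 0.40 read as a contrast of two equal groups (δ = 2f). If only half of the wounds above the threshold were lost, the attenuation at δ = 0.8 for p = 5%, 10% and 20% would be about 5%, 9% and 13%.

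**The case against.** A reader might infer that the rules as written remove poor healers from the wound comparison. The documents do not support that. The mandatory clause in 5.4.3 concerns an exclusion criterion that later comes to light, which most naturally means late discovery that someone was ineligible at entry. Section 5.6.1 attaches only documentation to medication use. The one explicit exclusion of data is for non-compliance with the nasal spray or its reporting. Section 5.7.3 does not say that people who discontinue leave the analysis of variance. Treated pain is also not the same as slow healing, and 7.3.2 calls inflammation and prolonged pain very rare. All of this stands, and it is why the point is put as a possibility.

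A reader might also infer that a woman on the pill is both excluded and expected. There is a coherent alternative: because sub-study 2 lists hormonal contraception separately from medication, the authors may not count the pill as medication, and it would then be allowed in sub-study 1. That reading is plausible, but neither 5.4.2 nor 5.6.1 states it.

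The treatment passages can likewise be read as a general ban with supervised exceptions. That may be the intent. The sentence in 5.6.1 contains no exception, so the wording still needs repair.

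Finally, analysis sets can be left to a statistical analysis plan, which is not at hand here. Attendance at the one-week visit cannot: a measurement that was never taken cannot be recovered at the analysis stage.

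**Conclusion.** Three things hold. The ban in 5.6.1 contradicts 7.3.2, section 9 and its own documentation sentence. The medication exclusion in 5.4.2 leaves the status of hormonal contraception open. No passage keeps a participant whose participation ends early in the one-week wound measurement, so outcome-related loss is possible, and group-mean replacement would not correct it.

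The statistical consequence is probably small. The protocol gives no frequency beyond very rare. Taking that as 1% of placebo participants or fewer, the model gives an attenuation of about 0.4% to 4% over the range shown (0.1% to 1%). The figures of 11% to 34% require an assumed 5% to 20%, which nothing in the protocol supports. All of these figures rest on normality, a sharp common threshold, and loss of every wound above it; the real effect may be negligible. The change is worth making because it protects the main outcome at almost no cost.

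**What to change.** 1. Reconcile 5.4.2, 5.4.3, 5.6.1, 7.3.2 and section 9 into one rule on other treatment. Which treatments are permitted is for the sponsor and investigator to decide.
2. State in 5.4.2 whether the medication criterion covers hormonal contraception, consistently with 7.3.3 and 7.3.4.
3. Add to 5.4.3 that treatment given after randomisation, or stopping the nasal spray because of an adverse event, does not end outcome collection. The participant is asked to attend the one-week wound measurement and is analysed in the allocated arm. The right to withdraw is unaffected.
4. Use the concomitant medication already recorded in the CRF for one sensitivity analysis that flags participants treated before that visit.

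The cost is a few sentences and one additional analysis. The small downside is that the outcomes of treated participants include the effect of their treatment, which the sensitivity analysis would help to show. Whether to adjust the cortisol analysis for pill use can be left to the statistical analysis plan.
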